#### Sample size

Assuming the rate of VF at 40%, a 95% confidence and 80% statistical power, sample size is 174 patients. Adding 10% potential LTFU during the one-year study period and 20% sequencing failure rate [10, 18], minimal sample size is 243 ADLHIV, rounded-up to 250 total sample size, further stratified into 150 ADLHIV in the referral centres (75 per site) and 100 in the HIV management units settings (50 per site), as per coverage in ART in these two geographical locations [41, 42].

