Laboratory procedures on sample management plans are provided below. Procedures at follow-up visits at months 6 and 12. Participants attending follow-up and their legal gauardians will be required to provide data contained in the follow-up Case Report Form, for updated information on epidemiological and clinical situation, with special emphasis on antiretroviral treatment information and HIV-related clinical events. Blood samples will be collected as described above. Similarly, for plasma viral load > 1000 copies/ml, adherence support will be provide then GRT performed if and only if virological failure is confirmed one-month later.All laboratory analysis will all be performed at the International Reference Centre Chantal Biya (CIRCB) in Yaounde, Cameroon, among which: Viral load measurementsWill be performed using Abbott m2000rt, as per the manufacturer’s instructions. Briefly, 600 μl of plasma collected from EDTA tube is used for viral RNA extraction. Based on the principle of reverse transcription polymerization (RT-PCR), amplicons are generated from the RNA genome of HIV-1 in clinical specimens. An RNA sequence that is unrelated to the HIV-1 target sequence is introduced into each sample at the beginning of sample PCR mix preparation. This unrelated RNA sequence is simultaneously amplified by RT-PCR, and serves as an internal control (IC) to demonstrate that the process has proceeded correctly for each sample. The amount of HIV-1 target sequence that is present at each amplification cycle is measured using fluorescent-labeled oligonucleotide probes on the Abbott m2000rt instrument. The amplification cycle at which an increase in fluorescent signal is detected by the Abbott m2000rt is proportional to the log of the HIV-1 RNA concentration present in the original patient sample.CD4/CD8 will be performed using FACSCalibur, as per the manufacturer’s instructions. Briefly, determination of lymphocyte subsets (CD3, CD4, CD8) will be performed on the flow cytometer (BD Biosciences, San Jose, CA) using a single-platform technology. A volume of 50 μl whole blood will be stained with 10 μl of Multitest reagent in Trucount tubes for 15 min (all from BD Biosciences), and red blood cells will be lysed by using fluorescence-activated cell sorting lysing solution (BD Biosciences). Data acquisition will be performed using CellQuest-Pro software (BD Biosciences) creating up to nine multicolor acquisition dot plots that use eight multicolor gates. Data will be then analyzed with FlowJo software version 7.5.5 for Microsoft (TreeStar, San Carlos, CA). Using Multitest reagents with Trucount tubes in the laboratory procedure, absolute subset count will be calculated with the following formula: (number of events in the region containing the cell population/number of events in the absolute count bead region) × (the number of beads per tube/test volume). If ncessary, a FACSCanto II (alternative platform to FACSCalibur) could be used for the same CD4/CD8 measurement purposes. Briefly, these analyses will be performed using the FACS Diva software (BD Biosciences, San Jose, CA), by reading information from the BD FACSTM 7-color setup beads label into BD FACSCanto clinical software (2D barcode symbology), and also by reading coded patient information into a worklist. Sanger Sequencing for HIV-1 drug resistance testing will be performed for adolescent experiencing virological faiure, using ABI 3130xl (Genetic Anlyser with 16 capillaries), HIV genotyping will be performed using plasma samples and an in-house reverse transcriptase polymerase chain reaction (PCR) protocol, as previously described (Fokam et al., 2011). Briefly, RNA will be extracted from 140 μl of concentrated plasma using the QIAamp Viral RNA minikit (Qiagen, Milan, Italy), according to the manufacturer’s protocol. RNA extracts will then be retrotranscribed and amplified using the kit One-Step Invitrogen (Foster City, CA) (SuperScript One-Step for long templates RT-PCR) and 2 different sequence-specific primers for 40 cycles. For insufficiently amplified samples after the first round PCR, a second round PCR (semi-nested PCR) will be performed. A direct sequencing reaction will be done using 7–8 overlapping primers. For a full plate run, the sequencer of 16 capillaries will analyse 2 different patient samples simultaneously for ~ 2.5 h per run, and assembly program (Seqscape v2.7) will be used for sequence analysis, and mutations will be interpreted following the Stanford HIVdb algorithm. Therefore, 12 samples will run for 15 h in total. Study timeline is provided as Additional file 1: (SDC) 1.

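### The 174 carries an 80% power claim with no stated difference, and the 20% sequencing-failure allowance is applied to the whole cohort although only confirmed virological failures are genotyped

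*Protocol article*

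**What the plan says.** The Sample size section of the protocol article opens with "Assuming the rate of VF at 40%, a 95% confidence and 80% statistical power, sample size is 174 patients". It names no null rate, comparison group, detectable difference or interval width. It then inflates this number: "Adding 10% potential LTFU during the one-year study period and 20% sequencing failure rate [10, 18], minimal sample size is 243 ADLHIV". The result is rounded up to 250 and split into 150 at the referral centres and 100 at the management units.

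Elsewhere the article fixes who contributes to each outcome:

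- Definition of study variables: VF is two consecutive plasma viral loads of at least 1000 copies/ml. No sequence is involved.
- Detailed procedures: resistance testing is conditional, "GRT performed if and only if virological failure is confirmed one-month later". The objectives at the end of the Background and the Procedures and timeline section likewise limit genotyping to participants with VF, at enrolment, month 6 and month 12, in plasma and buffy coat.
- Data collection and analysis: VF and HIVDR are described as prevalences with 95% confidence intervals. Both are also to be examined by site type, subtype, adherence and treatment line, with regression and survival models. VF is the primary outcome here and HIVDR a secondary one. The Abstract lists VF, HIVDR and mortality all as primary.

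**The concern.** A sample size for a proportion rests either on a target precision, which has no power term, or on a test, which needs a difference. The section claims "a 95% confidence and 80% statistical power" and supplies neither, so a reader cannot tell what the study is powered for.

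The inflation step then mixes two denominators. Sequencing failure cannot remove anyone from the VF analysis, so the 20% has no role in a number derived for VF. It does reduce the HIVDR analysis, but only among participants with confirmed VF, so the VF rate has to be applied first. As written, the allowance fits neither outcome.

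What is at stake is the account of HIVDR. The section appears to have provided for sequencing losses, yet it never says how many sequenced adolescents to expect or how precise the resistance estimates will be.

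**Working it through.** **Inputs from the Sample size section:** VF rate 40%; 95% confidence (taken as two-sided); 80% power; base 174; loss to follow-up 10%; sequencing failure 20%; total 243, rounded up to 250.

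**1. Reproduce the 243.** Dividing in turn and rounding up each time: 174/0.9 = 193.3, so 194; 194/0.8 = 242.5, so 243. This matches. Without intermediate rounding, 174/(0.9 × 0.8) = 241.7. The product 174 × 1.4 = 243.6 also lands close, but a 40% addition does not correspond to 10% and 20%. Successive division is the most plausible route, and it applies the 20% to all 174.

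**2. Try to reproduce the 174.** The stated inputs do not determine it.

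- Precision: 1.96 × √(0.40 × 0.60/174) = 0.0728. So 174 matches a 95% half-width of about 7.3 points, with no power term.
- One-sample test, same variance under both hypotheses: (1.96 + 0.842) × √(0.24/174) = 0.104, a difference of about 10.4 points.
- One-sample test of 40% against an assumed 30%: (1.96 × √0.21 + 0.842 × √0.24)²/0.10² gives 172.
- Two-sample test of 40% against an assumed 20%, 80% power, two-sided 5%: 164 in total at 1:1, and 168 or 172 at 3:2 depending on which group is larger.

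Several unstated choices come near 174. The tests tried do not give it exactly, and the article points to none of them. The basis is unknown.

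**3. VF outcome.** Only loss to follow-up applies: 174/0.9 gives 194. With 250 enrolled and 250 × 0.9 = 225 retained:

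- n = 250: 1.96 × √(0.24/250) = ±6.1 points
- n = 225: 1.96 × √(0.24/225) = ±6.4 points

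Both are tighter than the ±7.3 points at 174.

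**4. HIVDR outcome.** Participants with a usable sequence, per time-point and per compartment, are enrolled × retained × VF rate × 0.80:

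- Enrolment: 250 × 0.40 × 0.80 = 80
- Month 12: 250 × 0.90 × 0.40 × 0.80 = 72

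By contrast, the printed inflation would be right only if every participant were to be sequenced: 250 × 0.90 × 0.80 = 180.

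**5. HIVDR precision.** The article gives no design value for the resistance proportion. I assume 80%, the upper figure its Background mentions for mutations accumulating under delayed detection of failure. The half-width is 1.96 × √(0.80 × 0.20/n) = 0.784/√n.

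| Assumed VF rate | Sequenced, enrolment | Half-width | Sequenced, month 12 | Half-width |
|---|---|---|---|---|
| 20% | 40 | ±12.4 | 36 | ±13.1 |
| 40% | 80 | ±8.8 | 72 | ±9.2 |
| 47% | 94 | ±8.1 | 85 | ±8.5 |

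The 20% is the Background's figure for VF in children in resource-limited settings. The 47% is only a rough upper value: the Background gives it for children on second- or third-line treatment in another country who had VF with at least one major mutation, so it is not a VF rate for this cohort.

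**The case against.** **The power may belong to a planned comparison.** The analysis section does contain contrasts (site type, subtype, adherence, treatment line) and models, so it would be wrong to say that no analysis could use the 80%. This stands. What remains is that the comparison and its difference are not stated. A fuller protocol might give them, but the printed paragraph makes a power claim that cannot be checked against anything in the article.

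**The article never promises 174 sequences.** A reader might infer from the inflation step that resistance results should rest on 174 sequenced adolescents, and conclude that the design yields 72 to 80 instead. The documents do not support that contrast. The 174 is tied to the VF rate, and the article says openly that only participants with VF are genotyped.

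**72 to 80 is not the total yield.** Also correct. Genotyping is repeated at three time-points and done in two compartments. New failures during follow-up would add participants, and continuing failures would be sequenced again. The cumulative VF rate is not given, so the number of distinct participants sequenced over the year cannot be derived.

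**The primary outcome is safe.** In the analysis section VF is primary and HIVDR secondary. For VF the error only recruits more than needed, and the HIVDR intervals will show their own width when reported. This lowers the severity. It does not make the adjustment right, and the Abstract still lists HIVDR as primary.

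**Conclusion.** The point holds in two separate parts.

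First, the 80% power is attached to no stated null value, comparison or difference, and 174 cannot be reproduced from what is given. A half-width of about 7.3 points matches it, without any power term.

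Second, the 20% sequencing failure is applied to the wrong denominator. VF needs 194 on the plan's own base. For HIVDR the 250 enrolled imply about 80 participants with a usable plasma sequence at enrolment and about 72 at month 12, with a half-width of about 9 points at an assumed 80% resistance.

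These counts assume that the 40% refers to confirmed VF, that it still applies at month 12, and that the 20% failure rate holds at each visit. They are per time-point and per compartment.

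The VF estimate is not weakened. The section should be corrected, but this is not a must-fix: enrolment, procedures and the primary estimate are unaffected.

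**What to change.** Keep 250 and rewrite the Sample size paragraph:

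- Replace the 80% power claim with the VF precision (±6.1 points at 250, ±6.4 points at 225, at 40% VF). Alternatively, name the comparison and the difference that the power refers to and show that they give 174.
- Inflate the VF number for loss to follow-up only (174 to 194), and present 250 as exceeding it.
- Add a separate statement for HIVDR: the expected number of sequenced VF participants per time-point, with the 20% failure applied after the VF rate, and the resulting precision. Give it as a range over assumed VF rates, for example 40 at 20% VF and 80 at 40% VF at enrolment, and state the assumed resistance proportion.
- Say that these counts are per time-point and per compartment.

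The cost is one paragraph. No participants, visits or assays are added. The stated expectation for HIVDR becomes less favourable than the present wording suggests.

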#### Sampling strategy

All ADLHIV meeting study criteria will be invited for a written assent, as well as their legal guardians for a written informed consent. Fully consenting participants will be consecutively enrolled until complete sample size per site (75 for each of the two HIV referral centres and 50 for each of the two HIV management units). All participating ADLHIV will be consecutively assigned a unique ID number per site, and data will be centralised at the International Reference Centre Chantal Biya (CIRCB) for research on HIV/AIDS prevention and management in Yaounde, Cameroon. Physical and telephone contact details of participants will also be registered in the database for active follow-up, whenever necessary, by the study community-relay agents.

### Study procedures and variables

#### Procedures and timeline

Entire schedule requires 30-months overall: 6-months (month1–6) for administration/ethics/field preparedness, 6-months (Month 7–12) for enrolment of participants until complete sampling, 12-months monitoring (Month 7–24) for complete follow-up of one-year, and 6-months (Month 25–30) for closing study sites, data processing, and reporting. During enrolment (M0) at the clinic, study clinicians will obtain informed consent and participant assent from legal guardian and the ADLHIV, respectively, followed by collection of socio-demographic, clinical and economic data, HIV history (including date of HIV diagnosis and WHO-clinical staging), complete history of ARV (ART and/or PMTCT, previous viral load and CD4/CD8 whenever available), as well as adherence levels. Intravenous blood (6 ml) will be collected from each ADLHIV for laboratory analyses at the CIRCB. Practically, CD4/CD8 (cells/mm [3] and percentage) and plasma viral load (PVL) will be performed for all ADLHIV using flow cytometry and real-time polymerase chain reaction (PCR) respectively. Among those experiencing VF, RNA (from plasma) and DNA (from buffy coat) extracts, isolated using the QIAamp commercially available Viral RNA and DNA Mini Kit (QIAGEN), be will be used for PCR-amplification of the protease-reverse transcriptase (PR-RT) region of HIV-1. GRT will be performed on PR-RT amplicons using Sanger-sequencing, as previously described [43]. HIVDR-associated mutations will be interpreted using *Stanford HIVdb* algorithm [18, 35, 36, 43]. GRT results will then guide the selection of effective ARVs available in the national ART programme (first-, second-, and third-line regimens) and outcomes (WHO-clinical staging, viral and CD4/CD8 measurements) will be measured at 6 and 12 month-visits.

Follow-up visits will be at mid-point (months Month 6 [±1]) and at endpoint (Month 12 [±2]) after enrolment into the study. At each time-point (baseline, mid-point and end-point), epidemiological and clinical data will be collected using the same procedure described above during enrolment (i.e. baseline), including ART-adherence assessment. 6 ml of intravenous blood will be collected per visit (for CD4/CD8 and PVL). Among those experiencing VF at these visits, GRT will be performed as described above [18, 35, 36, 43], and the results will then guide the selection of effective ARVs available in the national ART programme for first-, second-, and third-line regimens.

At each study phase (enrolment, midpoint, endpoint), residual samples will be stored at − 80° available in the blood bank of the CIRCB. The entire work plan requires 30-months: 6-months (month1–6) for administration/ethics/field preparedness, 6-months (Month 7–12) for enrolment of participants until complete sampling, 12-months monitoring (Month 7–24) for complete follow-up of one-year, and 6-months (Month 25–30) for closing study sites, data processing, and reporting.

### Detailed procedures

At month-0, enrolment will be done at study clinic for all adolescents meeting study eligibility criteria. Participants will then be followed up during 12 months after enrolment, with scheduled visits at the clinic at months 6 (±1 month) and 12 (±2 month), for a total of 3 scheduled visits. Patients with virological failure (viral load > 1000 copies/ml) at any timepoint will undergo an extra visit in the next 1 month with adherence support and to confirm the virological failure (VF) as aforedescribed. Participants’ clinical management not considered in the study protocol will follow local recommendations for clinical practice at the discretion of the responsible physician.Procedures at Baseline visit (month 0). Mothers will be required to provide data contained in the Baseline Case Report Form (see clinical data definition below). Briefly, this will cover detailed epidemiological and clinical information, including socio-demographic and economic data, HIV history, history of antiretroviral usage by the adolescent, including drugs taken as part of PMTCT (if applicable), adherence to ART, and results from any laboratory test that were performed before study enrolment and available in the patient medical record file. Blood will be collected from each participating adolsecent, for a total of volumen 6 ml per timepoint for the following: determination of: viral load (600 μl plasma); CD4/CD8 levels (100 μl whole blood); HIV-1 Sanger sequencing for protease-reverse transcriptase (1000 μl plasma for RNA extraction and 200 μl buffy coat for DNA extraction); residual plasma samples will be stored at the biobank.

Laboratory procedures on sample management plans are provided below. Procedures at follow-up visits at months 6 and 12. Participants attending follow-up and their legal gauardians will be required to provide data contained in the follow-up Case Report Form, for updated information on epidemiological and clinical situation, with special emphasis on antiretroviral treatment information and HIV-related clinical events. Blood samples will be collected as described above. Similarly, for plasma viral load > 1000 copies/ml, adherence support will be provide then GRT performed if and only if virological failure is confirmed one-month later.All laboratory analysis will all be performed at the International Reference Centre Chantal Biya (CIRCB) in Yaounde, Cameroon, among which: Viral load measurementsWill be performed using Abbott m2000rt, as per the manufacturer’s instructions. Briefly, 600 μl of plasma collected from EDTA tube is used for viral RNA extraction. Based on the principle of reverse transcription polymerization (RT-PCR), amplicons are generated from the RNA genome of HIV-1 in clinical specimens. An RNA sequence that is unrelated to the HIV-1 target sequence is introduced into each sample at the beginning of sample PCR mix preparation. This unrelated RNA sequence is simultaneously amplified by RT-PCR, and serves as an internal control (IC) to demonstrate that the process has proceeded correctly for each sample. The amount of HIV-1 target sequence that is present at each amplification cycle is measured using fluorescent-labeled oligonucleotide probes on the Abbott m2000rt instrument. The amplification cycle at which an increase in fluorescent signal is detected by the Abbott m2000rt is proportional to the log of the HIV-1 RNA concentration present in the original patient sample.CD4/CD8 will be performed using FACSCalibur, as per the manufacturer’s instructions. Briefly, determination of lymphocyte subsets (CD3, CD4, CD8) will be performed on the flow cytometer (BD Biosciences, San Jose, CA) using a single-platform technology. A volume of 50 μl whole blood will be stained with 10 μl of Multitest reagent in Trucount tubes for 15 min (all from BD Biosciences), and red blood cells will be lysed by using fluorescence-activated cell sorting lysing solution (BD Biosciences). Data acquisition will be performed using CellQuest-Pro software (BD Biosciences) creating up to nine multicolor acquisition dot plots that use eight multicolor gates. Data will be then analyzed with FlowJo software version 7.5.5 for Microsoft (TreeStar, San Carlos, CA). Using Multitest reagents with Trucount tubes in the laboratory procedure, absolute subset count will be calculated with the following formula: (number of events in the region containing the cell population/number of events in the absolute count bead region) × (the number of beads per tube/test volume). If ncessary, a FACSCanto II (alternative platform to FACSCalibur) could be used for the same CD4/CD8 measurement purposes. Briefly, these analyses will be performed using the FACS Diva software (BD Biosciences, San Jose, CA), by reading information from the BD FACSTM 7-color setup beads label into BD FACSCanto clinical software (2D barcode symbology), and also by reading coded patient information into a worklist. Sanger Sequencing for HIV-1 drug resistance testing will be performed for adolescent experiencing virological faiure, using ABI 3130xl (Genetic Anlyser with 16 capillaries), HIV genotyping will be performed using plasma samples and an in-house reverse transcriptase polymerase chain reaction (PCR) protocol, as previously described (Fokam et al., 2011). Briefly, RNA will be extracted from 140 μl of concentrated plasma using the QIAamp Viral RNA minikit (Qiagen, Milan, Italy), according to the manufacturer’s protocol. RNA extracts will then be retrotranscribed and amplified using the kit One-Step Invitrogen (Foster City, CA) (SuperScript One-Step for long templates RT-PCR) and 2 different sequence-specific primers for 40 cycles. For insufficiently amplified samples after the first round PCR, a second round PCR (semi-nested PCR) will be performed. A direct sequencing reaction will be done using 7–8 overlapping primers. For a full plate run, the sequencer of 16 capillaries will analyse 2 different patient samples simultaneously for ~ 2.5 h per run, and assembly program (Seqscape v2.7) will be used for sequence analysis, and mutations will be interpreted following the Stanford HIVdb algorithm. Therefore, 12 samples will run for 15 h in total. Study timeline is provided as Additional file 1: (SDC) 1.

**Table Taba:** 

EWI and title	Definition	Numerator	Denominator	Target
EWI_1_ On-time pill pick-up	Proportion of adolescents that pick-up ART no more than two days late at the first pick-up after the baseline pick-up.	Number of adolescents picking-up their ART “on time” at the first drug pick-up after baseline pick-up date	Number of adolescents who picked-up ARV drugs on or after the designated EWI sample start date	Desirable performance (green): > 90%Fair performance (amber): 80–90%Poor performance (red): < 80%
EWI_2_ Retention in care	Percentage of adolescents known to be alive and on ART 12 months after enrolment	Number of adolescents who are still alive and on ART 12 months after enrolment	Total number of adolescents (excluding transfers out) who were expected to achieve 12-month outcomes	Desirable performance (green): > 85%Fair performance (amber): 75–85%Poor performance (red): < 75%
EWI_3_ Pharmacy stock-outs	Percentage of months in the study period in which there were no ARV drug stock-outs	Number of months in the designated year in which there were no stock-out, days of any ARV drug routinely used at the site	12 months of the reporting period	Desirable performance (green): 100%Poor performance (red): < 100%;
EWI_4_ Pharmacy dispensing practice	Percentage of adolescents being dispensed a mono- or dual-ART	Number of adolescents who pick up from the pharmacy, a regimen consisting of one or two ARVs;	Number of adolescents picking up ART on or after the designated EWI sample start date	Desirable performance (green) defined as 0% adolescents picking-up a mono- or dual-ARTPoor performance (red) defined as > 0% adolescents picking-up a mono- or dual-ART, and
EWI_5_ Virological suppression	Percentage of adolescents receiving ART of ART whose viral load is < 1000 copies/ml 12 months after enrolment	Number of adolescents receiving ART 12 months after study enrolment and whose viral load is < 1000 copies/ml	Number of adolescents who have a viral load performed at 12 months after enrolment	Desirable performance (green): > 85% Fair performance (amber): 70–85%Poor performance (red): < 70%

